## 2.2 Aims

**Aim 1:** Examine the efficacy of the VIDEO and VIDEO+CHW interventions on HbA1c (primary outcome) at 6 months

*Hypothesis:* We hypothesize that the VIDEO+CHW group will have the largest reduction in HbA1c, followed by the VIDEO group, and then the CONTROL group at 6 months.

**Aim 2:** Examine the efficacy of the VIDEO and VIDEO+CHW interventions on patient-centered outcomes (secondary outcomes) at 6 months. Secondary outcomes include enhanced self-efficacy, adherence to diabetes self-management behaviors, healthy eating, physical activity and medication taking.

*Hypothesis:* We hypothesize that the VIDEO+CHW group will have the greatest improvements in secondary outcomes, followed by the VIDEO group, and then the CONTROL group at 6 months.

**Aim 3 (exploratory):** To explore the long-term impact of the VIDEO and VIDEO+CHW interventions on HbA1c at 12 months

**Aim 4:** Examine the reach, adoption, fidelity, and maintenance of the VIDEO+CHW intervention within clinical and community settings, and use the implementation frameworks (RE-AIM, CFIR) to delineate contextual factors influencing implementation outcomes (Implementation Evaluation)

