#### 3.2 Sample and Sites

We will recruit 405 Chinese immigrants with uncontrolled T2D, who are currently receiving care at the Charles B. Wang Community Health Center (CBWCHC), a federally qualified health center located in both Manhattan Chinatown and Queens Chinatown. In 2020, CBWCHC provided a total of more than 233,000 service visits to more than 52,000 underserved Asian Americans in Greater NYC. The majority of patients are Chinese, limited English proficient (89%), and have an

income at or below 200% of poverty (84%). CBWCHC was chosen as our main recruitment site for several reasons: 1) there are existing collaborations with this site; [name] has been working with CBWCHC since 2016; 2) [name] is the Section Chief of Internal Medicine at the CBWCHC Queens Chinatown location and has clinical privileges at this site. He has been and will continue to act as a clinical site champion, and provide access to potential participants; and 3) CBWCHC is one of the largest and leading community centers in NYC, having established a trusting relationship with the Chinese American community

CBWCHC will not be engaged in research activities and their role is to identify/refer patients and provide space for this study. All research related activities (e.g. recruitment, consenting, conducting study procedures) will be performed by NYU study staff. The letter of support has been uploaded in the attachment section.

To maximize recruitment efforts, we will also identify potential private practices or community based organizations in Chinatown areas and work with them to recruit potential participants. In addition, we will identify and recruit participants into the study from NYU Langone Health. Similar to the procedures at CBWCHC, all of the research related activities (e.g. recruitment, consenting, conducting study procedures) will be performed by NYU study staff. The role of NYU Langone Health, these private practices or community-based organizations is to help to identify/refer patients and/or provide space for this study.

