**Table 2: RE-AIM and CFIR Evaluation Frameworks**

| CONSTRUCTS                                                                                                                                   | MEASURES (Quantitative/Qualitative)                                                                                                                                                                                               | DATA SOURCES                                                                                                    | TIME FRAME                                                                      |
|----------------------------------------------------------------------------------------------------------------------------------------------|-----------------------------------------------------------------------------------------------------------------------------------------------------------------------------------------------------------------------------------|-----------------------------------------------------------------------------------------------------------------|---------------------------------------------------------------------------------|
| REACH: What % of the target population came into contact with the program? Were participants representative of the target population? |                                                                                                                                                                                                                                   |                                                                                                                 |                                                                                 |
| Participants                                                                                                                                 | 
 
% patients with uncontrolled T2D
 
% patients at risk who received the VIDEO+CHW intervention
 
Representativeness of patients referred and participated in study
 
 | 
 
EHR data
 
In-depth interviews with providers and CHWs
 
 | 
 
Baseline, 6 months, 12 months
 
 |

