| Secondary Outcomes                                                                                                                                                                                                                                                                                                                                                  | • Change in HbA1c at 12 months and changes in self-efficacy,  diabetes self-management behaviors,  dietary intake,  physical activity,  medication adherence,  and SDOH  (at 6 and 12 months) | • Patient data from EHR
• Patient survey
• Healthify referrals                                                                                                                                                                        | • Baseline, 6 months, 12 months                                                                                                                                                               |                                                                   |
| ADOPTION: Did the organization use the program?                                                                                                                                                                                                                                                                                                              |                                                                                                                                                                                                                                                                                                     |                                                                                                                                                                                                                                             |                                                                                                                                                                                               |                                                                   |

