| Adoption                                                                                                                                                                                                                                                                                                                                                            | • Utilization patterns                                                                                                                                                                                                                                                                              | a) Provider, CBO, CHW interviews
b) Utilization reports (Redcap)
c) % of DSMES videos being watched; # of CHWs calls and duration of the call (Redcap)                                                                                | a) Baseline, 12 months
b,c) Weekly                                                                                                                                                         |                                                                   |
| IMPLEMENTATION (CFIR constructs to systematically guide identifying barriers/facilitators to implementation): How closely did staff members follow the program (consistency of delivery)? How well did the staff adhere to intervention fidelity? Was the program delivered as intended? Was the program consistent and aligned with clinic sites' missions? |                                                                                                                                                                                                                                                                                                     |                                                                                                                                                                                                                                             |                                                                                                                                                                                               |                                                                   |

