| CFIR                                                                                                                                                                                                                                                                                                                                                         | Intervention Characteristics/

Fidelity                                                                                                                                                                                                                                                       | a) % of staff attending trainings and orientations; utilization patterns
b) # DSMES videos watched by the patient
c) # CHW phone calls attended per patient and fidelity to the protocol
d) Utilization patterns of CHW case notes | a) Training log, trainee evaluations; Utilization reports (Redcap)
b) Video watch records (Redcap)
c) Fidelity checklist, CHW encounter logs (Redcap)
d) Redcap utilization records; | a) Baseline; Post training; 6 months
b,c) Monthly
d) Weekly |
|                                                                                                                                                                                                                                                                                                                                                                     | Characteristics of Individuals                                                                                                                                                                                                                                                                      | • Attitudes, norms, self-efficacy, and intention                                                                                                                                                                          | • Provider surveys                                                                                                                                                                            | • Baseline, 12 months                                             |

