| MAINTENANCE: Is the organization willing to sustain the program? Is the program able to become part of routine practice?                                                                                                                                                                                                                                     |                                                                                                                                                                                                                                                                                                     |                                                                                                                                                                                                                                             |                                                                                                                                                                                               |                                                                   |
| Practice patterns                                                                                                                                                                                                                                                                                                                                                   | • Current site patterns, barriers and facilitators                                                                                                                                                                                                                                                  | • Provider, CBO, and CHW interviews                                                                                                                                                                                                         | • 12 months                                                                                                                                                                                   |                                                                   |

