**Analytic Plan for Aim 4.** Utilizing the RE-AIM framework, we will address “reach” by comparing demographic and clinical characteristics of patients enrolled vs. eligible and not enrolled, using Wilcoxon’s rank-sum test or Fisher’s exact test. We will also examine these factors separately by sex and age brackets. To address “effectiveness”, we will use the random linear mixed modeling to examine whether the VIDEO+CHW intervention group had a greater reduction than the CONTROL group. For “adoption”, we will use Chi-square tests to compare the proportion of patients completing intervention components. To address “implementation”, we will report the frequency of barriers/facilitators to implementation, as well as other fidelity measures, and Chi-

square tests to compare proportions. Finally, both “implementation” and “maintenance” will be explored qualitatively as described below.

Barriers and facilitators to implementation of the VIDEO+CHW intervention. All interviews will be audio-recorded and transcribed. We will use “constant comparison” analytic approach. The “constant comparison” approach is a method of explanation building in which the findings of an initial case are compared to a provisional category, revised as necessary and then other details or new cases are then compared against the revision and revised again as needed. This process is continued until an area of interest is fully explicated, reaching theoretical saturation. Using “thematic” coding, we will develop an initial set of codes, which will be reviewed by the Steering Committee to ensure they are relevant and complete. For each core code, we will ultimately develop one or more “secondary codes” that represent either more specific or restricted aspects of the phenomenon, to contextualize it, or to suggest underlying meanings. The secondary codes will vary in specificity or subtlety depending on the judged substantive value of additional refinements. Transcripts will be coded by at least four coders (graduate and post-doctoral students). Discrepancies in coding will be discussed and resolved, then the process is repeated with a new set of transcripts until an acceptable level of inter-coder reliability between them has been achieved, estimated using an appropriate chance-corrected statistic (e.g., kappa for nominal data and T-index for ordinal data). We will use Atlas.ti software to analyze the transcripts.

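### Aim 4 analyses adoption through patient completion although Table 2 asks about organisations, and its only contact percentage for reach is capped by the 1:1:1 allocation

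*Protocol*

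**What the plan says.** Section 2.2 sets Aim 4 as follows: "Examine the reach, adoption, fidelity, and maintenance of the VIDEO+CHW intervention within clinical and community settings". Table 2 then gives a guiding question, measures and data sources for each RE-AIM dimension, and the Aim 4 paragraph of section 7.1 gives the analyses.

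- **Adoption.** The guiding question in Table 2 is "Did the organization use the program". The sources are "Provider, CBO, CHW interviews" at baseline and 12 months, REDCap utilisation reports, and patient-level records of videos watched and of the number and duration of CHW calls. The analysis in 7.1 is: "we will use Chi-square tests to compare the proportion of patients completing intervention components".
- **Fidelity.** Under implementation, Table 2 lists the number of videos each patient watched and the number of "CHW phone calls attended per patient and fidelity to the protocol".
- **Reach.** Table 2 asks what percentage of the target population the program touched and whether participants were representative. It lists three measures: the percentage of patients with uncontrolled T2D, the percentage of "patients at risk who received the VIDEO+CHW intervention", and representativeness. For reach, 7.1 compares the demographic and clinical characteristics of enrolled patients with those of eligible patients who did not enrol.
- **Qualitative work.** 7.1 assigns qualitative exploration to implementation and maintenance. Adoption is not named there.

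**The concern.** The unit of the adoption question is the organisation; the unit of the adoption analysis is the patient. A patient can watch every video whether many clinics took part or only one. The pilot described in section 2.1 had a mean watch rate of 92% in 30 people. A similar figure here could be reported as high adoption with no information on how many providers or organisations took up the program.

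For reach, the difficulty is the quantity chosen. The share of patients receiving one randomised arm is limited by the allocation ratio before anyone is approached. Reported as the answer to the contact question, it would describe the trial design more than the program.

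Both matter because the follow-up interviews in section D4.2 are meant to inform replication and scaling to other sites, and these two dimensions feed that discussion.

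**Working it through.** Aim 4 states no sample size, target or percentage of its own, so there is no plan figure to reproduce beyond the allocation in section 3.1: three arms of 135, and 3 × 135 = 405, which agrees with the stated total.

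**Adoption: question against analysis**

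1. Unit of the question (Table 2): the organisation.
2. Unit of the only analysis named for adoption (7.1): the patient, classified by completion of components.
3. Overlap: videos watched and CHW calls appear under both adoption and fidelity in Table 2. The test in 7.1 therefore draws on quantities that already serve another dimension.
4. Comparison groups: 7.1 does not name them. By Table 1, CONTROL has no intervention components and VIDEO has no calls. If arms are what is compared, the only available contrast is video completion in VIDEO against VIDEO+CHW. If the groups are something else, the unit is still the patient. In neither case does the test show whether an organisation used the program.
5. Interviews: listed as an adoption source in Table 2, and section D4.2 says the follow-up interviews cover the adoption process. The analytic plan does not connect them to adoption. D4.2 plans surveys of 10 participating physicians and interviews with 15 key informants; neither comes with a denominator of sites or providers approached.

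**Reach: the ceiling on the receipt measure**

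Inputs: 135 allocated to VIDEO+CHW and 405 enrolled (section 3.1). Let *f* be the fraction of eligible patients who enrol. The protocol does not give *f*, so a range is assumed.

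- Share of enrolled patients receiving VIDEO+CHW ≤ 135 / 405 = 33.3%.
- Share of eligible patients receiving VIDEO+CHW ≤ *f* × 135 / 405 = *f* / 3.

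| Assumed *f* (enrolled / eligible) | Ceiling on receipt of VIDEO+CHW |
|---|---|
| 100% | 33.3% |
| 50% | 16.7% |
| 30% | 10.0% |
| 10% | 3.3% |

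The left column is what an enrolled-over-eligible measure would report; the receipt measure reports at most a third of it.

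Of the other two reach measures, the percentage with uncontrolled T2D describes the population and not contact with the program, and representativeness is a comparison of characteristics. The analysis in 7.1 serves representativeness and returns no contact percentage. The percentage question in Table 2 is therefore left with the capped measure alone.

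**The case against.** The strongest reply is that Table 2 and D4.2 already supply what seems to be missing. Adoption has an organisation-level source: interviews at baseline and 12 months, with questions adapted from validated measures that include adoption and organisational culture, and 7.1 describes coding for all interviews. This stands, and a reader who inferred that adoption has no organisation-level data would be wrong. What remains is that the analytic plan names a patient-level test for adoption and leaves the interviews unattached to it.

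On reach, a reader might infer that the protocol defines it solely as receipt of one arm. It does not: there are three measures, and 7.1 already compares enrolled patients with eligible non-enrolled patients across all arms. That comparison addresses who came in, not what percentage did. It can also be said that the one-third ceiling follows openly from the design and would mislead no informed reader. That limits the harm but does not make the measure informative.

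The unnamed groups for the chi-square test could be settled in a statistical analysis plan that is not shown. This is fair, and the silence on groups is not counted as an error here.

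**Conclusion.** The point holds for adoption and for one reach measure. The adoption analysis is at the wrong level for the adoption question, and the only contact percentage for reach cannot exceed 33.3% of enrolled patients, or one third of the enrolled fraction among eligible patients. The ceiling assumes the planned equal allocation is achieved; the range for eligible patients rests on assumed enrolment fractions.

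A reader might go further and conclude that maintenance cannot be answered either, because section 3.2 says "CBWCHC will not be engaged in research activities and their role is to identify/refer patients and provide space for this study". The documents do not support that. The maintenance questions look forward ("Is the organization willing to sustain the program? Is the program able to become part of routine practice"), the 12-month interviews and qualitative analysis suit them, and no observed sustained delivery by sites is claimed. Nor does the protocol say who employs the CHWs, so it cannot be stated that community organisations have no part in delivery.

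Nothing here touches the primary outcome, its type I error or the sample size. It is a correction worth making in the implementation aim.

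**What to change.** 1. **Adoption (7.1 and Table 2).** Report video and call completion under implementation/fidelity. Assess adoption at organisation and provider level, using the interviews already planned together with the share of approached clinics, providers and community organisations that referred at least one patient.
2. **Reach (Table 2 and 7.1).** Replace the receipt-of-VIDEO+CHW measure with enrolled divided by eligible patients approached, all arms combined, and keep the existing representativeness comparison beside it.

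**Cost.** Mostly wording in Table 2 and one paragraph of 7.1. The reach ratio can draw on the screening counts that section 4.2 keeps for the CONSORT diagram. The adoption share needs a short log of the organisations and providers approached. The protocol does not show that one is kept: the initial referral lists in section 4.1 hold only patient names and phone numbers. Participant burden and the efficacy aims do not change.
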